### Statistical plans

#### Sample size

Our sample size was chosen to ensure adequate power to detect significant differences in the primary study outcome, IDS-C, between the intervention arm and enhanced usual care. We plan to enroll both sexes, but we anticipate 85% of participants to be female; thus, power considerations are stratified by sex. The project will enroll 274 adults (226 women, 48 men; ages 18–65 years) who meet previously described eligibility criteria.

To determine study sample size, we assumed a two-sided 5% type-I error rate, standard deviation of up to 14 units for the IDS-C (according to preliminary data on the IDS-self report), and a meaningful difference across arms of six points on average on the IDS-C [58]. Analyses will use linear mixed effects models with random effects for blocks and fixed effects for treatment assignment. Since participants will be enrolled in groups of approximately 15 at a time and intervention will be delivered in a group setting, there is a possibility of an intra-cluster correlation (ICC). Previous literature has suggested that ICC tends to be low in group intervention studies, so here we considered ICC values 0.001–0.01 [91]. Under these assumptions, eight groups of women per arm (each of size 12; i.e., 96 women per arm) or 192 women total would ensure 84% power to detect a meaningful difference across arms. To combat anticipated 15% study attrition, we plan to enroll 226 women [59]. Power analyses were conducted via simulation in the R programming language (version 4.1.1) and verified using PASS (version 15) [92]. Note that our initial design and power analyses involved cluster randomization rather than block randomization. Because cluster randomized trials tend to have lower power, our original power analyses suggested 240 women would be required for 80% power, and thus, opting for block randomization reduces the number of participants required.

Additionally, we plan to enroll two groups of men, each of size approximately 12 (i.e., 48 men). We do not anticipate that we will have adequate power to detect meaningful differences across arms in men, and thus, analyses in men will be hypothesis-generating and assess feasibility in this population.

Though our power is greater than 80% for our primary aim, we anticipate an ultimate sample size of 192 women provides 80% power to detect small to moderate standardized effect sizes (*d*≥0.4) in secondary outcomes under the same assumptions. With respect to correlation coefficients (since partial correlation coefficients will play a role in mediation analyses), we will have 80% power to detect a correlation coefficient of 0.2 at the 5% level in either the overall sample or just in women, and a correlation coefficient of 0.39 or larger in men.

#### Statistical analyses

Proportions, means, medians, and ranges will be used to summarize baseline distributions of demographic factors and clinical mental health presentation (i.e., baseline depression, anxiety, trauma, stress) at baseline stratified by study arm. Exploratory data analyses will be conducted wherein individual trajectories of each primary and secondary study outcome over 6 months by study arm are visualized.

##### Primary outcome analyses

We intend to conduct all primary statistical analyses according to the intention-to-treat (ITT) principle. We will estimate the average treatment effect for participants classified by study arm, independent of participation in any M-Body classes. This approach is conservative because it protects the effect of randomization from confounding introduced by subject dropout and crossover. We will employ both a classic ITT analysis as well as a modified ITT analysis, wherein all participants completing at least one follow-up visit will be included, regardless of adherence. This will allow us to understand the bias introduced by study dropout.

The primary outcome analysis will consist of a linear mixed model (LMM) in which mean 6-month IDS-C will be compared across study arms (fixed effect), controlling for gender, baseline IDS-C scores, and baseline receipt of psychotherapy, the variables upon which randomization is stratified. We will include a random group effect as this is an individually randomized group-treated design. This approach will account for within-group associations to more precisely estimate intervention effects. The coefficient for study arm will address the question: “for two patients with the same baseline depressive symptoms, gender, and baseline receipt of psychotherapy, if one is given the M-Body intervention and the other enhanced usual care, will the patients have different depressive symptoms after 6 months?”

As a sensitivity analysis, we will estimate the average treatment effect among the treated. This analysis will allow us to estimate among individuals randomized to the intervention whether there is a dose-effect relationship between the number of classes attended and depressive symptoms. This analysis, done only in the intervention arm, will consist of a LMM in which 6-month IDS-C will be regressed upon the number of M-Body sessions attended (fixed effect), controlling for gender, baseline IDS-C scores, and baseline receipt of psychotherapy, and as before, including a random group effect. The coefficient on number of sessions attended will address the question: “on average, what is the difference in six-month IDS-C that attending one more M-Body session affords, holding gender, baseline IDS-C score, and baseline receipt of psychotherapy constant?”

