##### Secondary outcome analyses

We will conduct four exploratory secondary outcome analyses, one each for depression, anxiety, anger, and trauma, designed to leverage the longitudinal nature of outcome assessment in this study. The first will consist of a LMM in which IDS-C will be compared across study arms at each follow-up visit (three fixed effects), controlling for gender, baseline IDS-C scores, and baseline receipt of psychotherapy. Here we will include random effects for group participation and individual, as we will need to account for within-person correlation. We will consider a simpler model for parsimony including follow-up visit as a continuous variable, as in a linear growth mixed effects model, and select the model that minimizes the Bayesian Information Criterion. The visit-specific coefficients on study arm will address the question: “for two patients with the same baseline depressive symptoms, gender, and baseline receipt of psychotherapy, if one is given the M-Body intervention and the other enhanced usual care, will the patients have different depressive symptoms after 2, 4, and/or 6 months?” The secondary outcome analyses for GAD and anger will use similar models to those described here for IDS-C, this time additionally including baseline GAD or anger scores as appropriate. The secondary outcome analysis for trauma will consist of a linear mixed model (LMM) in which mean 6-month trauma will be compared across study arms (fixed effect), controlling for gender, baseline IDS-C scores, and baseline receipt of psychotherapy, with a random group effect. If issues with model convergence are encountered, we will consider simpler models, such as a linear model with fixed effects for groups, or a linear model with no group effects specified. No interim analysis is planned or will take place; we do not anticipate study developments to require interim analyses.

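### Comparing classic with modified ITT cannot reveal dropout bias when the primary model uses only the 6-month IDS-C and no imputation is shown

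*Protocol article*

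**What the plan says.** Under Primary outcome analyses, the protocol article commits to ITT and describes two versions. One is a classic ITT, whose handling of missing outcomes is not described. The other is a "modified ITT analysis, wherein all participants completing at least one follow-up visit will be included, regardless of adherence". The reason given for running both is: "This will allow us to understand the bias introduced by study dropout".

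The same section fixes the primary model. In it, "mean 6-month IDS-C will be compared across study arms (fixed effect"). The adjustment terms are three baseline variables: gender, IDS-C score and whether psychotherapy was being received. On clustering the section adds: "We will include a random group effect as this is an individually randomized group-treated design". There is no participant-level random effect, and the 2- and 4-month IDS-C scores do not appear.

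Those interim scores enter only under Secondary outcome analyses, in a model labelled exploratory: "The first will consist of a LMM in which IDS-C will be compared across study arms at each follow-up visit". That model has random effects for group and individual. It may be replaced by a model linear in time if the BIC prefers it.

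On expected losses, the Sample size section says: "To combat anticipated 15% study attrition, we plan to enroll 226 women".

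**The concern.** A population defined by at least one follow-up visit makes sense for a longitudinal model, because each visit then supplies data. Paired with a model whose only outcome is the 6-month score, it does not change who is analysed. A participant seen only at 2 or 4 months is counted as included but adds nothing to the estimate.

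Two things are at stake. First, the report could show two identical estimates and offer their agreement as evidence that dropout did no harm, when agreement was guaranteed. Second, an estimate labelled ITT would be a completer estimate. Participants know their assignment, and only one arm attends weekly classes and is contacted after missed sessions, so dropout that differs by arm cannot be excluded. The 2- and 4-month scores could help correct for dropout related to interim symptoms, but the primary analysis does not use them.

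**Working it through.** **1. The plan's own figures.** Inputs from Sample size: two-sided 5%, SD 14, difference 6, 96 women per arm, ICC 0.001 to 0.01, attrition 15%.

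- SE = 14 × √(2/96) = 2.02. Power = Φ(6/2.02 − 1.96) = Φ(1.01) = 84.4%, or 84.0% with the t distribution.
- Design effect 1 + 11 × ICC: at ICC 0.001, power is 84.0% with both arms clustered and 84.2% with only the intervention arm clustered. At ICC 0.01 it is 80.5% and 82.4%.
- Enrolment: 192 / 0.85 = 226 women.

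The stated 84% and 226 reproduce; the lower power at ICC 0.01 does not bear on this point.

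**2. Expected losses.** 226 − 192 = 34 women. The article states no attrition for the 48 men. If 15% applied to them too, 0.15 × 274 = 41 of 274 would lack the outcome and about 233 would have it.

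**3. Who enters the primary fit.** The stated model is

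Y6 = β0 + β1·arm + β2·gender + β3·baseline IDS-C + β4·psychotherapy + group effect + error.

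A participant with no Y6 contributes nothing to this likelihood. Counting the phone assessment as a follow-up visit, and without imputation:

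| Follow-up pattern | Classic ITT set | Modified ITT set | Enters the fit |
|---|---|---|---|
| 6-month IDS-C observed | yes | yes | yes |
| 2- and/or 4-month only | yes | yes | no |
| No follow-up | yes | no | no |

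The last column is the same for both sets, so the two estimates are equal. This needs no assumption about why people leave.

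**4. Numerical confirmation.** Simulated trials with assumed inputs: N = 274, true effect −6, SD 14, within-person correlation about 0.5, about 14% missing at 6 months, dropout depending on the 2-month score in opposite directions by arm, 25 replicates.

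- Largest difference between classic and modified estimates: 0.0.
- On average 261 participants met the modified definition and 236 entered the fit, so about 25 were included in name only.
- Mean estimate from the stated model: −7.02 (Monte Carlo SE 0.31). From a longitudinal model on all three visits: −6.21 (0.32).

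**5. Size of the bias left unseen.** Assumed inputs: 137 per arm, SD 14, visit correlation 0.6 (also 0.5 to 0.7), about 14% to 15% missing at 6 months, logit slope 0.9 per SD of the 4-month IDS-C, 2,000 to 4,000 trials per setting. There is no true effect; a negative bias favours M-Body.

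| Dropout related to 4-month score | Completer bias (points) | Type I error |
|---|---|---|
| Same direction in both arms | 0.00 to +0.03 | 4.5% to 5.4% |
| One arm only | −0.3 to −0.45 | about 6% |
| Opposite directions by arm | −0.7 to −0.9 | 8% to 9% |

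Check on the error rates, from bias/SE:
- −0.87/1.49 = −0.58, giving Φ(−1.38) + Φ(−2.54) ≈ 0.09.
- −0.41/1.47 = −0.28, giving Φ(−1.68) + Φ(−2.24) ≈ 0.06.

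In the opposite and one-arm settings, an estimator that also used the 2- and 4-month scores had bias of at most 0.06 points. With a true 6-point effect and same-direction dropout, completer bias was 0.11 to 0.15 points toward zero.

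**The case against.** The strongest reply is that the article does not say how the classic ITT treats a missing 6-month score. An imputation rule may sit in the full protocol or SAP, which are not shown. This stands: the exact identity is conditional on there being no imputation, and the absence of a rule in an article is not itself a fault. It does not rescue the check. If the classic set alone were imputed, the gap between the two estimates would mainly reflect the imputation model. The modified fit would still ignore people lost between months 2 and 6.

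Three further points also stand in part.

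- Baseline adjustment handles dropout explained by gender, baseline IDS-C and baseline psychotherapy. It does so equally in both analyses, so the comparison gains nothing.
- A baseline-adjusted model at a single time point is a recognised choice and matches the stated endpoint. The exploratory longitudinal model, if not displaced by the BIC rule, would show a 6-month contrast beside it.
- Same-direction dropout produces essentially no bias under the null.

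A reader might infer that the primary result will be biased, or that the type I error is 9%. The documents do not support either. They contain no evidence on the direction of dropout or on whether interim scores predict it, and the 9% belongs to the most adverse setting examined.

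**Conclusion.** The stated model and the stated purpose of the two ITT analyses do not fit together. Without imputation of the 6-month IDS-C, the classic and modified estimates coincide exactly and carry no information about dropout bias. With imputation of the classic set only, their difference still would not measure it.

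The consequence for the treatment effect depends on an unknown mechanism. Under the assumptions in step 5 and no true effect, it runs from about 0 to about −0.9 points, or 15% of the 6-point target (0.9/6). This should be fixed because the remedy is cheap and uses data already being collected. It does not show that the primary analysis is invalid.

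**What to change.** By formal amendment, before any arm-level outcome data are examined:

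1. Take the 6-month arm contrast from the longitudinal IDS-C model in Secondary outcome analyses as the single primary test. Use months 2, 4 and 6, visit fixed as categorical with no BIC choice, arm-by-visit terms, within-person correlation, and the same covariates and group effect.
2. Keep the 6-month-only model as a sensitivity analysis.
3. Replace the classic-versus-modified comparison, as the dropout check, with a delta-adjusted multiple-imputation sensitivity analysis that includes all randomised participants. This matters because people with no follow-up also contribute nothing to the longitudinal model when baseline is a covariate.

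The endpoint, sample size and data collection do not change. The cost is some extra analysis work and a documented late change to the primary model. That change needs a clear record, since the Randomization section leaves the statistical team unblinded and Trial status reports 232 of the planned 274 already randomised.

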#### Participant eligibility

Participants will be eligible to enroll in the study if they are between the ages of 18 and 65 years, fluent in English, and enrolled in care at a FQHC and have score greater or equal to 5 on the PHQ-9, which indicates mild depressive symptoms. Exclusion criteria will include a suicide attempt in the past 30 days; endorsement of severe suicidal thoughts on the PHQ-9 (item 9); a current meditation practice defined as four or more sessions per week; or employment at the FQHC. Mental health treatment (individual or group psychotherapy and psychiatric medication) is permitted for the duration of the trial.

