### Randomization

Following consent but prior to randomization, participants will complete a clinical interview and baseline surveys, and stress biomarker data will be collected. We will then implement a block randomization procedure, with each participant in a cohort randomly assigned to 1 of the 2 arms (overall allocation ratio, 1:1). Block randomization with randomly varying block sizes was chosen to prevent prediction of assignments and thereby protect from selection bias. Randomization will be stratified by gender, initial severity of depression (Inventory of Depressive Symptomatology- Clinician Administered (IDS-C) ≥38), and receipt of treatment for depressive symptoms (antidepressants and/or psychotherapy versus none) [62]. To avoid all possibility of interference from the investigators, randomization will be fully automated, with the randomization sequence prespecified in R [63] and implemented through Research Electronic Data Capture (REDCap) [64, 65]. After randomization, research staff will provide participants with a sealed envelope containing their condition assignment. Neither the participants, study coordinators, statistical analysis team, nor the treatment providers will be blinded to treatment assignments. Independent evaluators and study co-investigators will remain blinded. To maintain the overall quality and legitimacy of the clinical trial, unblinding should occur only in exceptional circumstances when knowledge of the actual treatment is absolutely essential for further management of the participant. The Principal Investigator will discuss with the co-investigators and DSMB if she believes that unblinding is necessary.

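### The models adjust for psychotherapy at baseline and call it a stratification variable, but randomisation was stratified on antidepressants and/or psychotherapy

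*Protocol article*

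**What the plan says.** The Randomization section names three stratification factors. It begins "Randomization will be stratified by gender, initial severity of depression" (IDS-C of 38 or more) and ends with "receipt of treatment for depressive symptoms (antidepressants and/or psychotherapy versus none". The third factor is therefore a composite: either treatment, or both, against neither.

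Primary outcome analyses describes the main linear mixed model as "controlling for gender, baseline IDS-C scores, and baseline receipt of psychotherapy, the variables upon which randomization is stratified". Its arm coefficient is then interpreted "for two patients with the same baseline depressive symptoms, gender, and baseline receipt of psychotherapy".

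Secondary outcome analyses repeats the term. For the longitudinal depression model, "IDS-C will be compared across study arms at each follow-up visit (three fixed effects), controlling for gender, baseline IDS-C scores, and baseline receipt of psychotherapy". For trauma, "controlling for gender, baseline IDS-C scores, and baseline receipt of psychotherapy, with a random group effect". The anxiety and anger models are said to be similar, each with its own baseline score added.

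Participant eligibility states: "Mental health treatment (individual or group psychotherapy and psychiatric medication) is permitted for the duration of the trial".

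**The concern.** The primary analysis section does more than list covariates. It says that they are the stratification variables, and for the treatment factor this does not match the Randomization section. Anyone treated with antidepressants but not psychotherapy falls on different sides of the two definitions.

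Two things are at stake. The first is precision: stratifying on a prognostic factor balances it between arms, but the model-based standard error reflects that balance only if the factor is in the model. The second is pre-specification. The text supports two primary models, one that follows the named covariate and one that follows the claim that the covariates are the stratification factors. The Randomization section says that the statistical analysis team is not blinded, so the choice should be settled before outcomes are analysed.

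**Working it through.** **1. Are the two terms the same variable?** The psychotherapy-only term appears seven times. Four are in Primary outcome analyses (the main model, its question, the dose-effect model, its question). Three are in Secondary outcome analyses (the longitudinal IDS-C model, its question, the trauma model). Neither section mentions antidepressants, and nothing in the article defines psychotherapy to include them. Participant eligibility lists psychotherapy and psychiatric medication as separate things and permits both, so participants on medication only can exist. Side by side:

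| Baseline treatment | Stratum at randomisation | Model covariate, read literally |
|---|---|---|
| Neither | none | no |
| Psychotherapy, with or without antidepressants | treated | yes |
| Antidepressants only | treated | **no** |

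**2. Does the stated power depend on it?** Inputs from Sample size: 96 women per arm, difference 6, SD 14, two-sided 5%.
- SE = 14 × √(2/96) = 2.02; 6/2.02 = 2.97; power = Φ(2.97 − 1.96) = 84.4%.
- With a design effect of 1 + 11 × ICC in both arms, power is 84.0% at ICC 0.001 and 80.5% at ICC 0.01. With clustering in the intervention arm only, it is 84.2% and 82.4%.
- Attrition: 192/0.85 = 225.9, so 226.

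The stated 84% reproduces, at the low end of the ICC range. No covariate enters it, so it stands whichever treatment variable is used.

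**3. How much precision could be lost?** The article gives neither the share of participants treated nor the prognostic effect of treatment. Assume a proportion p = 0.4 treated and a treated-untreated difference δ of 0.3 to 0.5 residual SD at 6 months. The share of residual variance explained is p(1 − p)δ²:
- δ = 0.3: 0.4 × 0.6 × 0.09 = 0.022
- δ = 0.5: 0.4 × 0.6 × 0.25 = 0.060

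Omitting the factor altogether widens the SE by about half that share, so about 1% to 3%. In participants:
- 192 analysable women: 0.022 × 192 ≈ 4 to 0.060 × 192 ≈ 12
- completers, 274 × 0.85 ≈ 233: 0.022 × 233 ≈ 5 to 0.060 × 233 ≈ 14

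This prices complete omission. The plan keeps psychotherapy, one component of the composite, so under these inputs the true loss is smaller.

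**4. Simulation of the actual swap.** Assumptions, none from the article: 35% on antidepressants and 25% in psychotherapy, independent of each other; baseline-outcome correlation 0.5; no group effect; n = 192; 3,000 runs. Each row compares the psychotherapy covariate with the composite stratum.

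| Assumed effect on IDS-C (antidepressant, psychotherapy) | Mean estimate | SD of estimate | Power |
|---|---|---|---|
| 0, 0 | −6.01 vs −6.01 | 1.722 vs 1.716 | 93.1% vs 93.4% |
| 4, 4 | −6.02 vs −6.02 | 1.783 vs 1.772 | 91.5% vs 92.1% |
| 8, 4 | −5.98 vs −5.98 | 1.814 vs 1.791 | 90.2% vs 91.9% |

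The true effect was −6. Type I error was 0.040 to 0.050 with psychotherapy and 0.039 to 0.055 with the composite. Power exceeds 84% here because the simulation adjusts for baseline IDS-C; only the differences within rows matter.

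**The case against.** The strongest reply is that the shorter term is shorthand. The sentence that names the covariates also says that they are the stratification factors, and in the same breath it writes baseline IDS-C scores for a factor randomised as a cut at 38. A condensed article may well abbreviate. This stands in part: no coding specification is shown, so one cannot say that antidepressant-only participants will be coded untreated, only that they would be if the text is followed literally. It does not remove the contradiction. The term recurs seven times, and the article elsewhere separates psychotherapy from medication.

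A second reply is that little harm follows, and this stands. The models as described are linear with no arm-by-covariate interaction, so conditioning on either variable targets the same mean difference between arms, and only precision changes. The largest simulated power gap, 1.7 points, needs an assumed 8-point antidepressant effect, which is larger than the 6 points that the plan calls meaningful. Nothing in the article shows that treatment status is prognostic once baseline IDS-C is in the model.

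A reader might also price the loss on the 274 enrolled, which gives 0.022 × 274 ≈ 6 to 0.060 × 274 ≈ 16 participants. The plan does not support that figure: it expects 15% attrition, and it does not drop the factor entirely.

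Finally, the dose-effect model uses the M-Body arm only and is not a randomised comparison. The argument from stratified precision does not reach it.

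**Conclusion.** The contradiction is certain on the face of the article: the covariate called a stratification variable is not the one defined under Randomization. Its consequence is modest. A reader might infer that the primary estimate is biased or the trial underpowered, and neither follows: the arm comparison stays unbiased, simulated type I error was near nominal, and the 84% does not depend on the covariate.

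What remains is a small loss of precision of unknown size. The upper bound of about 1 to 3% on the standard error rests on the assumed 40% treated and 0.3 to 0.5 SD difference. The primary model is also left open to two readings. This should be corrected, but it does not threaten the trial's validity. Using continuous baseline IDS-C in place of the severity cut is acceptable and is not part of the mismatch.

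**What to change.** In the primary and secondary between-arm models, and in the questions used to interpret their coefficients, replace the psychotherapy covariate with the treatment stratum as randomised (antidepressants, psychotherapy or both, against neither). Keep gender and continuous baseline IDS-C. If the Randomization section misdescribes the factor actually used, correct that section instead. Either way the sections must agree.

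In the dose-effect model the same covariate may be used for consistency and to help control confounding of attendance, but stratification precision is not the reason.

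The cost is a wording change and one variable in the code. Randomisation ran through REDCap, so the stratum should already be recorded. The article describes the trial as ongoing, with data collection to end in June 2023; on that timeline the change can be made before the outcome analysis.

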### Study aims

This study is a two-arm group-treated individually randomized controlled trial to test the clinical effectiveness of a mindfulness-based intervention (M-Body) on reducing depressive symptoms among socio-economically disadvantaged, predominantly Black women in an FQHC. The M-Body intervention will be led by trained FQHC staff; fidelity to the intervention, adherence, and competence will be continuously assessed. Feedback on factors relevant to the implementation of the intervention in the FQHC, including attitudes toward implementation of intervention, implementation leadership, and attitudes toward adoption and clinical effectiveness of evidence-based practices, will be obtained by convening quarterly workgroups and individual semi-structured interviews with FQHC staff and leadership.

Our specific aims and corresponding hypotheses are to:Examine the effectiveness of a mindfulness-based intervention (M-Body) compared to enhanced usual care on reducing depressive symptoms over a 6-month period among racial/ethnic minority adults at a Federally Qualified Health Center (FQHC).*H1a: We hypothesize that participants in the M-Body arm will experience a significantly greater reduction in depressive symptoms than those in the enhanced usual care arm.**H1b: We hypothesize that greater class attendance in the M-Body intervention will be associated with a greater reduction in depressive symptoms.*Conduct a broad assessment of organization and individual agency factors related to the implementation of the M-Body intervention at a FQHC using a mixed methods approach.

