### Retention and adherence strategies

To enhance recruitment and recognize the contributions of participants in the UC condition, these individuals will be invited to participate in the M-Body group at the end of 6 months after all data have been collected. To improve engagement in the intervention, the research staff will phone, email, or text subjects whenever they miss a session to encourage participation. Reminders will be sent to all participants to remind them of upcoming data collection and the incentives they will receive. The study team will make every effort to be flexible and accommodate participant schedules.

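### The planned effect among the treated is a slope on sessions attended within the M-Body arm: it has no untreated comparison, is open to confounding, and is worded causally

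*Protocol article*

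**What the plan says.** All of the relevant text is in the protocol article.

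- **Label.** Primary outcome analyses: "As a sensitivity analysis, we will estimate the average treatment effect among the treated".
- **Model.** The same paragraph says the analysis is "done only in the intervention arm, will consist of a LMM in which 6-month IDS-C will be regressed upon the number of M-Body sessions" attended, "controlling for gender, baseline IDS-C scores, and baseline receipt of psychotherapy, and as before, including a random group effect". The control arm is not used.
- **Reading of the coefficient.** It is meant to answer "what is the difference in six-month IDS-C that attending one more M-Body session affords", with the three covariates held constant.
- **Protection by randomisation.** The section claims this for the intention-to-treat analysis, on the ground that "it protects the effect of randomization from confounding introduced by subject dropout and crossover". It gives no matching caveat for the attendance analysis.
- **Hypothesis on attendance.** Study aims, H1b: "We hypothesize that greater class attendance in the M-Body intervention will be associated with a greater reduction in depressive symptoms".
- **Control access.** Under Retention and adherence strategies, usual-care participants are "invited to participate in the M-Body group at the end of 6 months after all data have been collected". The Control arm section agrees.
- **Unmeasured causes.** The limitations paragraph of the Discussion accepts that the stressors affecting this population are only partly measured. It expects them to influence both engagement in the study and psychological outcomes.

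**The concern.** An effect among the treated compares people who received treatment with what would have happened to the same people without it. That needs information on untreated outcomes, and in this trial the randomised control arm supplies it. A regression confined to the M-Body arm discards that information and compares frequent with infrequent attenders. No sample size turns this into the named quantity.

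The comparison is also not randomised. Work, stress, motivation and early response can all drive attendance, and each may also bear on 6-month IDS-C. Gender, baseline IDS-C and baseline psychotherapy need not capture them.

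At stake is how one prespecified supporting result is interpreted. Reported under its present label, an adherence association would be presented as a causal effect and as a check on the main finding. It is neither.

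**Working it through.** **Label against model.**

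| | Effect among the treated | Analysis as specified |
|---|---|---|
| Comparison | treated versus the same people untreated | more versus fewer sessions |
| Participants | both arms needed | M-Body arm only |
| Source of validity | randomisation, with an exclusion restriction | no unmeasured confounding of attendance |
| Robustness check on the primary contrast | related to it | answers a different question |

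**Inputs.** The plan states no figure for this analysis, so there is none to reproduce. From the Sample size section: IDS-C SD 14, meaningful difference 6, 96 women per arm analysed. These are consistent with the stated 84% power: 6/14 x sqrt(96/2) = 2.97, and 2.97 - 1.96 = 1.01, which gives 84.4% before clustering. Mean attendance in the staff-led pilot groups was 5.9 sessions (Prior work). The correlations and the session SD below are assumptions, because the article gives neither.

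**Size of the bias under a true null.** Let an unmeasured factor U, independent of the adjustment variables, have correlation r with sessions and -r with 6-month IDS-C. With zero effect of sessions:

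slope = covariance / variance of sessions = -(r x r x 14) / session SD

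| r | session SD 2.3 | session SD 1.5 | session SD 3.0 |
|---|---|---|---|
| 0.2 | -0.56/2.3 = -0.24 | -0.37 | -0.19 |
| 0.3 | -1.26/2.3 = -0.55 | -0.84 | -0.42 |
| 0.4 | -2.24/2.3 = -0.97 | -1.49 | -0.75 |

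For scale, if a 6-point difference were linear in sessions at the pilot mean, the true slope would be -6/5.9 = -1.02 per session.

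**Direction.** The sign follows the two correlations. If U raises attendance and lowers IDS-C, the slope falsely suggests benefit. If participants who improve stop attending, low attendance goes with low scores, and the slope is pushed towards no benefit or apparent harm.

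**Simulation.** 2000 trials per scenario with zero true effect, sessions limited to 0 to 8 (mean about 5.8), adjustment for baseline score, and no group clustering. False benefit means a significant negative slope (nominal 2.5%).

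| r | mean slope, n = 96 | false benefit, n = 96 | false benefit, n = 116 |
|---|---|---|---|
| 0 | 0.0 | 2.9% | 2.4% |
| 0.2 | -0.28 | 5.4% | 5.6% |
| 0.3 | -0.61 | 14.0% | 19.9% |
| 0.4 | -1.14 | 42.4% | 47.9% |
| 0.5 | -1.80 | 80.1% | 85.6% |

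Here 116 is 274/2 x 0.85. Slopes are a little steeper than in the formula because capping at 8 sessions narrows the spread. On the same data the randomised comparison rejected in about 4.5% to 5.1% of trials (nominal 5%). An instrumental estimate using assignment averaged between -0.01 and +0.02 per session. That shows freedom from this confounding under the null; it does not test the exclusion restriction.

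**What assignment can identify.** By design, controls attend no sessions before month 6. Under the exclusion restriction:

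arm difference = proportion of the M-Body arm attending at all x effect among attenders

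So the effect among the treated is the arm difference divided by that proportion. This holds for a binary exposure (any attendance). With session count as exposure, the estimate is essentially the arm difference divided by mean sessions. That is a weighted per-session effect and needs a linear dose assumption to be read as the value of one more session.

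**The case against.** The best defence is that the model suits the question the paragraph goes on to ask: whether, among those assigned to M-Body, outcome varies with classes attended. H1b is framed as an association, and a within-arm regression can describe one. This stands. The model is acceptable for H1b; the faults are the treatment-effect label, the sensitivity-analysis tag and the causal verb. Holding three covariates constant does not cure them.

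A second objection is that the size of the bias is hypothetical. This also stands. The correlations and session SD are not in the article, the bias is small at r = 0.2, any part of U captured by the covariates would reduce it, and only one direction was simulated. Nor should a per-session slope be multiplied by eight and set against the 6-point arm difference. That contrasts no attendance with full attendance, which is not the quantity in the sample size calculation.

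A third objection is that an instrumental estimate cannot show whether more sessions help more. That is correct, and it is why the within-arm regression should be kept for H1b.

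A reader might infer that the slope will be offered as evidence for H1a as though randomisation protected it. The article does not say so. The between-arm question belongs to the intention-to-treat model, and protection by randomisation is claimed only there.

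**Conclusion.** The label and the model do not match, and this follows from the text without any assumed number. The analysis is a within-arm association between attendance and 6-month IDS-C. It does not estimate an effect among the treated and does not probe the robustness of the primary contrast.

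Confounding is a realistic threat. The Discussion accepts partly measured stressors acting on both engagement and outcome, although it speaks of engagement in the study rather than attendance specifically. Under the stated assumptions (r of 0.2 to 0.4, session SD 2.3, true null) the spurious slope is about -0.24 to -0.97 points per session. False benefit then occurs in roughly 5% to 42% of trials with 96 in the arm. These figures are illustrations, not predictions.

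Two stronger conclusions are not supported. A false benefit is possible but not certain, since the bias could equally hide one. The primary intention-to-treat estimate and its test are untouched.

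**What to change.** 1. Keep the within-arm regression for H1b only, labelled an exploratory observational association. Remove the treatment-effect label, the sensitivity-analysis tag and the verb affords, and state that attendance is not randomised.
2. If an effect among the treated is to be reported, estimate it in all randomised participants, with assignment as instrument, any attendance (yes/no) as exposure and the same covariates. Allow for clustering by M-Body group with a small-sample correction, because the Trial status section expects only 16 courses.
3. State the exclusion restriction and its weak point. Under Participation incentives, all M-Body participants receive the manual and audio. Under the COVID-19 modifications, the manual is mailed before the first session. Someone who attends nothing may still be affected by these materials.
4. A sessions-based instrumental estimate may be added, described as a weighted per-session effect that relies on a linear dose assumption.

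The cost is a change of wording and one extra model on data already being collected. The instrumental interval will be wider, and it carries an assumption that the intention-to-treat analysis does not need.
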